## Abstract

**Background:**

Antibiotic resistance is an individual and public health problem; multidrug-resistant infections could cause an estimated 10 million deaths worldwide by 2050. Unnecessary use of antimicrobials is the most important cause of resistance generation in the community, and an estimated 80% of antimicrobials are prescribed in primary health care, frequently for urinary tract infections (UTIs).

**Objective:**

This paper presents the protocol for the first phase of the Urinary Tract Infections in Catalonia (Infeccions del tracte urinari a Catalunya) project. We aim to examine the epidemiology of the different types of UTIs in Catalonia (an autonomous community in Spain) and their diagnostic and therapeutic management by health professionals. Furthermore, we aim to evaluate the correlation between types and total consumption of antibiotics for recurrent UTIs in 2 cohorts of women with the presence and severity of infectious complications of urological origin, especially pyelonephritis and sepsis, and 2 potentially serious infections: pneumonia and COVID-19.

**Methods:**

The study is a population-based observational cohort study including adults with a diagnosis of UTI registered in the Information System for the Development of Research in Primary Care (in Catalan: Sistema d’informació per al desenvolupament de la investigació en atenció primària), the Minimum Basic Data Sets of Hospital Discharges and Emergency Departments (in Catalan: Conjunt mínim bàsic de dades a l’hospitalització d'aguts i d’atenció urgent), and data from the Hospital Dispensing Medicines Register (in Catalan: Medicació hospitalària de dispensació ambulatòria) of Catalonia from the period between 2012 and 2021. We will evaluate the variables obtained from the databases to analyze the proportion of different types of UTIs, the percentage of adequate antibiotic treatments prescribed or received for recurrent UTIs according to the national guidelines, and the proportion of UTIs with complications.

**Results:**

We expect to describe the epidemiology of UTIs in Catalonia from 2012 to 2021, as well as describe the diagnostic and therapeutic management of UTIs by health professionals.

**Conclusions:**

We expect to find a high percentage of UTI cases with inadequate management according to the national guidelines, considering that on many occasions UTIs are treated with second- or third-line antibiotic therapies with a preference for the longest regimens. Furthermore, the use of antibiotic suppressive therapies, or prophylaxis, in recurrent UTIs will likely be highly variable. Moreover, we aim to determine whether women with recurrent UTIs treated with antibiotic suppressive therapies have a higher incidence and severity of potentially serious future infections, with special attention to acute pyelonephritis, urosepsis, COVID-19, and pneumonia, compared to women who receive antibiotic treatment after they present with a UTI. This is an observational study of data from administrative databases that will not allow causality analysis. The limitations of the study will be handled according to the appropriate statistical methods.

**Trial Registration:**

European Union Electronic Register of Post-Authorisation Studies EUPAS49724; https://www.encepp.eu/encepp/viewResource.htm?id=49725

**International Registered Report Identifier (IRRID):**

DERR1-10.2196/44244

## Introduction

It is estimated that 10 million people could die worldwide by 2050 from infections caused by multidrug-resistant pathogens if urgent measures are not taken to combat the problem of antimicrobial resistance, mainly among gram-negative bacteria and especially enterobacteria [1]. Antibiotic resistance is an individual health and public health problem; increasing community resistance can prolong the infectious process, increase the risk of infecting other individuals, and in the long term, lead to increased costs. Inappropriate use of antibiotics increases the frequency of related and sometimes serious side effects and causes increased mortality [2,3]. Unnecessary use of antimicrobials is the most important cause of resistance generation in the community, and it is estimated that 80% of antimicrobials are prescribed in primary health care (PHC) [4].

Urinary tract infections (UTIs) are a common infection in PHC, and most patients are treated with antibiotics [5-7]. In Spain, UTIs represent the second most frequent cause of antibiotic prescriptions [8]. Almost 60% of women experience at least one episode during their lifetime [9,10]. Antibiotic treatment of uncomplicated UTIs is, in most cases, empirical, and the selection of the antimicrobial is made according to the most frequently involved pathogen and local resistance. Several studies have suggested that up to 50% of antibiotic prescriptions are inappropriate [11-13]. There is a tendency to use broad-spectrum antibiotics, which do not usually provide substantial improvements in efficacy over narrower-spectrum antibiotics and instead favor increased resistance [4].

Approximately 80% of cases of uncomplicated UTI are caused by *Escherichia coli*, so empirical treatment should cover this pathogen [14-16]. The resistance of uropathogens to classical antibiotics has increased significantly in recent years in Spain [17]. Various studies in Spain have described resistant *E coli* infections and shown that a high percentage are resistant to penicillins. A study published in 2017 that was conducted in our setting among patients with community-acquired pyelonephritis showed that 23% were resistant to ciprofloxacin, while 1% were resistant to fosfomycin [18]. In the program of surveillance of nosocomial infections in the hospitals of Catalonia (Vigilància de les infeccions nosocomials als hospitals de Catalunya [VINCat; all non-English abbreviations are in Catalan unless otherwise noted]), a local database from Catalonia (an autonomous community in Spain) that is part of the Antimicrobial Optimization Program (Programa d’optimització de l’ús d’antimicrobians [PROA]), it was shown that in 2020 *E coli* had a high sensitivity to fosfomycin (96.6%) and nitrofurantoin (98.5%); by contrast, its sensitivity to the amoxicillin/clavulanic acid combination, cotrimoxazole, and quinolones was much lower (75%, 74%, and 72%, respectively) [19]. Resistance of enterobacteria to third-generation cephalosporins, mediated by the production of extended-spectrum β-lactamases, is a growing problem in *E coli* and *Klebsiella pneumoniae* strains. Data from the VINCat PROA 2020 report show that the proportions of β-lactamase-producing *E coli* and *K pneumoniae* urinary tract infections in the community in Catalonia were 9% and 11%, respectively [19]. UTIs caused by resistant microorganisms are associated with longer symptom duration than infections caused by sensitive strains, and treatment is more likely to fail [20].

According to the recommendations of the Infectious Diseases Society of America, empirical antibiotherapy should not be used when resistance rates exceed 20% for all strains [21]. This means that the use of combined amoxicillin/clavulanic acid, as well as quinolones and cotrimoxazole, should no longer be recommended for empirical treatment of UTIs in our country. Current guidelines in PHC recommend prescribing a single dose of 3 grams of fosfomycin trometamol or nitrofurantoin for 5 to 7 days [22,23]. The rationale for this strategy is to specifically target the etiologic agents causing acute cystitis based on knowledge of the local resistance patterns to antimicrobials of the most frequent uropathogens [24]. In recent years, the use of fosfomycin as the therapy of choice for these infections has increased significantly in Spain. However, more than half of all physicians prefer the use of short-course therapies to single doses [25]. One of the reasons mentioned by professionals for not giving first-line treatments is to prevent complications, the most frequent being acute pyelonephritis; however, there is currently no predictive scale available to determine the risk that a UTI will worsen to pyelonephritis. Only 26% of antibiotic prescriptions for uncomplicated UTI were for fosfomycin trometamol (3-gram single dose) or nitrofurantoin in primary care management in Barcelona in the entire year 2020 (unpublished data).

Another dilemma faced by practitioners is the recommendation to give suppressive antibiotic treatment lasting more than 6 months to women who have repeated UTIs (defined as more than 2 UTIs in the last 6 months or more than 3 in the last year) [26]. However, this practice is not exempt from potential risks. In a recent article, a clear correlation was reported between a history of antibiotic use in the previous 2 years and the severity of COVID-19 (with severity defined as a variable combining death, hospitalization, and the presence of pneumonia), based on data from the Information System for the Development of Research in Primary Care (Sistema d’informació per al desenvolupament de la investigació en atenció primària [SIDIAP]) [27]. This correlation was very strong when antibiotics were taken in the previous 2 months, when there were more than 5 antibiotic regimens in the last 2 years, and when antibiotics were used that are critical and should be reserved for special cases, such as cephalosporins and quinolones. In addition, prudent use of antibiotics is necessary due to the increase in antibiotic resistance [3,28].

Urine culture requests are not always made according to guidelines. As early as 2000, it was documented that 44% of requests were made for cases of asymptomatic bacteriuria, a condition for which they should not be ordered and there should be no treatment [29]. In 2014, 92% of urine cultures that were ordered for a second time for patients with a UTI were not necessary [30]. In 2019, a range of 21% to 42% of requests for urine cultures were for uncomplicated UTIs in Barcelona city primary care management (in Spanish: gerencia *de atención primaria de Barcelona ciudad*), depending on the primary care center (unpublished data). The ordering of urine cultures for women with cystitis is only recommended in cases of (1) uncomplicated cystitis that, despite adequate antibiotic treatment, remains symptomatic (posttreatment urine cultures are used), (2) recurrent cystitis (pretreatment urine cultures are used), and (3) cystitis in pregnancy (both pretreatment and posttreatment urine cultures are used) [14]. The use of these tests when they are not necessary leads to antibiotic overprescription; moreover, since in many cases they are requested for cases of bacteriuria in elderly people who have been treated with antibiotics many times, the results of antibiograms recommend the prescription of second-line antibiotics for uropathogens that are often multidrug-resistant.

For all the above reasons, we propose the current protocol for the Urinary Tract Infections in Catalonia (Infeccions del tracte urinari a Catalunya [ITUCAT]) study, consisting of 4 work packages (WPs) that will be implemented successively in 3 phases, to evaluate different objectives related to UTIs in the adult population in Catalonia and investigate specific aspects of this condition in this population. The first phase of the project, which is presented in this paper, includes the first 2 WPs. WP 1 will evaluate the management of UTIs in Catalonia, and WP 2 aims to evaluate the correlation of antibiotic use for repeated UTIs with the presence of infectious complications in adult women. Subsequently, we will carry out the second phase with the data obtained from the first phase. At this stage, the aim is to create a scale to predict acute pyelonephritis in patients with UTI by evaluating clinical variables; this will be WP 3. Finally, in the third phase, we will perform WP 4, which aims to determine the degree of inadequacy in requests for urine cultures based on clinical practice guidelines and to establish the basis for a training intervention.

The study described in this paper corresponds to the first phase, which includes WP 1 and WP 2.

## Methods

### Study Design and Population

This is a population-based observational cohort study. The inclusion period was from January 1, 2012, to December 31, 2021. The study population was patients aged ≥18 years with a diagnosis of UTI registered in SIDIAP during the study period. UTI diagnoses included the International Statistical Classification of Diseases and Related Health Problems, 10th Revision (ICD-10) codes (Table 1).

**Table 1 table1:** Health problems included in the study and their International Statistical Classification of Diseases and Related Health Problems, 10th Revision codes.

ICD-10 codes	Health problems
N10	Acute tubule-interstitial nephritis
N30	Cystitis
N30.0	Acute cystitis
N30.1	Interstitial cystitis (chronic)
N30.2	Other chronic cystitis
N30.3	Trigonitis
N30.8	Other cystitis
N30.9	Cystitis, unspecified
N34	Urethritis and urethral syndrome
N34.1	Nonspecific urethritis
N34.3	Urethral syndrome, unspecified
N39.0	Urinary tract infection, site not specified
N41	Inflammatory diseases of prostate
N41.0	Acute prostatitis
N41.1	Chronic prostatitis
N41.3	Prostatocystitis
N45	Orchitis and epididymitis
N45.0	Orchitis, epididymitis, and epididymo-orchitis with abscess
N45.9	Orchitis, epididymitis, and epididymo-orchitis without abscess

### Data Collection and Data Sources

The data needed to carry out the project will be obtained from the SIDIAP database, the Minimum Basic Data Sets (Conjunt mínim bàsic de dades [CMBD]) of Hospital Discharges and Emergency Departments (Conjunt mínim bàsic de dades a d’hospitalizació d’aguts [CMBD-HA] and Conjunt mínim bàsic de dades d’atenció urgent [CMBD-UR], respectively) registries, and data from the Hospital Dispensing Medicines Register (Medicació hospitalària de dispensació ambulatòria [MHDA]).

The SIDIAP contains pseudonymized clinical information from the Electronic Health Records in Primary Care (Estació clínica d’atenció primària) program [31], which is the electronic health records program for PHC of the Catalan Health Institute (Institut català de la salut [ICS]) in Catalonia. The ICS manages 279 PHC centers, covering a population of 5.8 million people (approximately 80% of the Catalan population). Among this adult population, information is available for more than 3384 PHC medical staff members.

The information recorded in SIDIAP contains sociodemographic data; health conditions, coded by ICD-10 [32]; clinical parameters; tobacco and alcohol use; diagnostic procedures; PHC laboratory test results; specialists’ referrals; and prescriptions of PHC medical staff, with the corresponding pharmacy billing data, registered as anatomical, therapeutic, chemical (ATC) classification system codes [33]. Several reports have shown that SIDIAP data are useful for epidemiological research [34,35]. SIDIAP is listed under the European Network of Centres for Pharmacoepidemiology and Pharmacovigilance resources database [36].

The CMBD is a population-based registry that collects information on pathologies treated in the health centers of Catalonia [37] and includes ICD-10 codes [32]. This registry contains information provided by all Catalan health care centers on health care activity and morbidity. The CMBD-HA contains information on acute hospitalizations, with reasons and dates for hospital admission. The CMBD-UR reports activity in emergency departments.

The MHDA is a registry containing information on specific drugs that are dispensed in hospitals and reimbursed by the Catalan health system [38,39].

### Sample Size

A feasibility count was requested from the SIDIAP database for the years 2012 and 2021. It was estimated that approximately 2.5 million UTIs were registered in the Catalan population during the study period.

### Variables

Variables included in WP 1 and WP 2 include sociodemographic information; clinical variables and health conditions, with ICD-10 codes; tobacco and alcohol use; PHC laboratory test results; vaccination status (for influenza, pneumococcus, and COVID-19); prescriptions, with their corresponding pharmacy invoice data registered as ATC codes [33] in addition to prescriptions for MHDA drugs [38,39]; dates of sickness leaves, visits, and referrals (to second- and third-level centers); sexual and reproductive health care; CMBD-HA hospital information; and CMBD-UR emergency department information (Multimedia Appendix 1).

### Study End Points

#### Primary End Points

The primary end points of the first phase for WP 1 are the proportion of different types of UTI (uncomplicated UTIs, recurrent UTIs, and pyelonephritis), the percentage of first-line antibiotics used for different types of UTI according to the national guidelines [40,41], and the percentage of inappropriate prescriptions, with the type of antibiotic of these prescriptions. The primary end points for WP 2 are the percentage hospitalization rate and the proportion of UTIs with complications (ie, pyelonephritis, sepsis, pneumonia, and COVID-19). COVID-19 infection will be determined by ICD-10 codes, tests (ie, polymerase chain reaction tests, rapid antigen tests, and others), or both.

#### Secondary End Points

The secondary study endpoints are (1) types of UTI in women aged ≥18 years with the percentage of recurrent UTIs (defined as more than 2 UTIs in the last 6 months or more than 3 episodes in the last year); (2) types of UTI in men aged ≥18 years; (3) the percentage of urine cultures and laboratory tests ordered for the different types of UTI in both men and women; (4) the percentages of different types of antibiotics used in patients with UTIs, as well as dosage and duration of treatment; (5) the percentage of women with recurrent UTIs who were treated with suppressive therapy (ie, antibiotic treatment 3 times a week for 6 months or more) and the duration of the therapy; (6) the percentage of infectious complications, especially acute pyelonephritis and sepsis, in the 2 cohorts (ie, women with recurrent UTIs with suppressive therapy and women with recurrent UTIs without suppressive therapy but with UTIs treated punctually; (7) the percentage of pneumonia and COVID-19 infection in the 2 cohorts (ie, women with multiple antibiotic regimens for UTIs or suppressive therapy and women with UTIs treated punctually); and (8) the frequency of clinical variables of people affected by UTI who progress to acute pyelonephritis.

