### Statistical Analysis

Demographic and baseline characteristics of the participants will be reported as frequencies and percentages for categorical variables and means and standard deviation or median and interquartile range for continuous variables, as appropriate.

For WP 1, descriptive statistics will be reported for the results. For WP 2, a severity variable will be constructed that will include mortality and hospitalization, in addition to the presence of pneumonia in cases of COVID-19. Quantitative variables will be described as means and standard deviation, while categorical variables will be described as the proportion of exposed and unexposed individuals. Univariate tests will include the Student *t* test and the chi-square test, as appropriate. For the primary outcome, marginal structural models will be fitted to estimate causal effects by correcting for confounders. Inverse probability weights will be estimated as a function of propensity score using sociodemographic variables and clinical variables. The inverse probability weights will be used in the marginal structural model to estimate the risk ratio and confidence intervals for the prevalence of each outcome among individuals exposed to antibiotics versus those not exposed to antimicrobials. During the assessment of the correlation of prior antibiotic exposure with the different outcomes, patients will only be counted once and assigned to the worst outcome (with the severity of COVID-19 ranked in decreasing order as death, hospitalization, and pneumonia). The Wald test will be used to determine whether the adjusted risk ratios are significantly different from zero at a significance level of 5%.

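### Suppressive therapy is defined by completed duration, so unless time zero is aligned the comparison with punctually treated women can be biased toward apparent protection

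*Protocol article*

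**What the plan says.** In the protocol article, Secondary End Points item 5 asks for the percentage of "women with recurrent UTIs who were treated with suppressive therapy (ie, antibiotic treatment 3 times a week for 6 months or more". Item 6 then compares pyelonephritis and sepsis between "women with recurrent UTIs with suppressive therapy and women with recurrent UTIs without suppressive therapy but with UTIs treated punctually". Item 7, on pneumonia and COVID-19, uses a different split: "women with multiple antibiotic regimens for UTIs or suppressive therapy and women with UTIs treated punctually".

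Under Statistical Analysis, for WP 2, "a severity variable will be constructed that will include mortality and hospitalization". The weighted model is to give the "risk ratio and confidence intervals for the prevalence of each outcome among individuals exposed to antibiotics versus those not exposed to antimicrobials", and each patient is counted once, at her worst outcome. On adjustment: "Inverse probability weights will be estimated as a function of propensity score using sociodemographic variables and clinical variables".

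The article gives no index date, landmark or time-varying exposure. It has no rule for women who start a suppressive regimen and stop, have a complication or die before 6 months. Its limitations paragraph covers underreporting, unlinked diagnoses and treatments, and unmeasured confounding, but not time-related bias.

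**The concern.** Membership of the suppressive cohort depends on treatment that accrues after therapy starts. To qualify, a woman must survive and stay on treatment for 6 months. Those months are event-free by construction for death, and for any complication that ends therapy. If they also count as follow-up, the exposed cohort is credited with time in which it could not have such an event.

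The outcomes include death, hospitalization, sepsis and pyelonephritis, some of which can prevent a woman from reaching month 6. Weights built from sociodemographic and clinical variables address who is likely to be treated, not follow-up time assigned to the wrong cohort. A risk ratio for prevalence does not split person-time either. The Discussion asks whether suppressive therapy brings more, and more severe, infections. A bias toward protection would hide or shrink that signal, and the roughly 2.5 million UTIs in the feasibility count would not dilute it.

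**Working it through.** The article gives no figure for this bias, so there is none to reproduce. The check asks what risk ratio the duration rule produces when suppressive therapy has no effect (true RR = 1).

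**From the article:** exposure requires 6 completed months; the effect measure is a risk ratio; outcomes include death; the inclusion period is 2012 to 2021, with follow-up per woman not stated.

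**Assumed, not in the documents:** constant event rate λ = 0.05 or 0.20 per year; share starting suppressive therapy f = 10% or 30%; share stopping before 6 months for unrelated reasons d = 30%; share of early events that end therapy q = 1 (always true of death), 0.5 or 0; follow-up T years from therapy start, or from a matching date in comparators.

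**Formulas**
- Risk by T: p = 1 − exp(−λT). Risk in the first 6 months: e = 1 − exp(−0.5λ).
- Starters who complete 6 months: C = (1 − d)(1 − q·e). Completers with an event by T: E = (1 − d)(p − q·e).
- Suppressive risk: E / C.
- Comparator risk if early stoppers join the comparator: (p − f·E) / (1 − f·C). If they join neither cohort: p.

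**Worked case** (λ = 0.05, f = 0.3, T = 1, q = 1)
- p = 0.0488, e = 0.0247
- C = 0.7 × 0.9753 = 0.6827; E = 0.7 × (0.0488 − 0.0247) = 0.0169
- Suppressive risk = 0.0169 / 0.6827 = 0.025
- Comparator risk = (0.0488 − 0.3 × 0.0169) / (1 − 0.3 × 0.6827) = 0.055
- Apparent RR = 0.449 (from unrounded values)

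**Apparent RR over both values of λ and f, true RR = 1**

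| Follow-up | q = 1, stoppers in comparator | q = 1, stoppers in neither | q = 0.5, stoppers in comparator | q = 0 |
|---|---|---|---|---|
| 1 year | 0.449–0.509 | 0.506–0.525 | 0.711–0.762 | 1.00 |
| 2 years | 0.715–0.775 | 0.759–0.786 | 0.855–0.892 | 1.00 |
| 5 years | 0.890–0.935 | 0.911–0.939 | 0.945–0.969 | 1.00 |
| 9 years | 0.945–0.978 | 0.955–0.979 | 0.972–0.989 | 1.00 |

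Leaving early stoppers out of both cohorts does not remove the bias.

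**Earlier time zero.** This was a simulation of 2 million women followed from meeting the recurrent-UTI definition. It assumed that 30% start therapy, spread over the next 12 months (6 months at the 1-year horizon), with q = 1, no other stopping, and non-completers counted as comparators. The apparent RR was 0.195–0.214 at 1 year, 0.431–0.484 at 2 years and 0.765–0.840 at 5 years. The wait before therapy adds further event-free time.

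**Check of the remedies.** With therapy start as time zero, assignment at start gave RR 0.994–1.008 and a common 6-month landmark gave 0.995–1.009. The remedies were not simulated with delayed starts, which is why the comparators need a matched date.

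**The case against.** A reader might infer that early deaths and complications necessarily fall into the comparator cohort, so that suppressive therapy will look protective. The article does not support that much, for these reasons:

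- **Time zero is not given.** The Statistical Analysis section describes antibiotic exposure as preceding the outcome, and the Discussion speaks of infections in the future. Both fit counting outcomes only once exposure is complete. A condensed article may also leave index dates to the full protocol or SAP. This stands, and makes the bias conditional. Even so, a valid comparison needs the same survival and time condition in the comparator, and the article does not state one.
- **Only death necessarily blocks month 6.** A non-fatal complication does so only if it ends therapy, and nothing says that it does. This stands; with q = 0 there is no bias.
- **Early stoppers may belong to neither cohort.** The comparator must also have been treated punctually. This stands as a reading, but the bias survives it.
- **Long follow-up dilutes the effect.** This stands, although women who qualify late in the inclusion period may have little follow-up.
- **The link to the weighted model is loose.** That model is for the primary outcome and contrasts exposure with no exposure to antibiotics. The 6-month rule sits in the secondary end points and covers only part of the exposed cohort in item 7. This narrows the point mainly to item 6.
- **Net direction is uncertain.** Confounding by severity could push the ratio above 1. That would not cancel the design problem in any predictable way.

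The Introduction's "suppressive antibiotic treatment lasting more than 6 months" differs slightly from the threshold in item 5. That is a minor wording difference and no part of this point.

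**Conclusion.** The concern holds in conditional form. The article fixes the suppressive cohort by completed duration, and nothing it states prevents the resulting event-free time from counting. If follow-up starts at or before therapy start, item 6, and in part item 7, can be biased toward protection.

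The bias could be large at 1 to 2 years if early events usually end therapy. It is modest by 5 years with follow-up from therapy start and absent if early events never end therapy. These sizes rest on assumed rates, uptake and stopping shares, so they show a plausible range and do not predict this study's result. That suppressive therapy will in fact look protective is not established.

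**What to change.** State time zero for both cohorts and how women who stop before 6 months are handled. Then choose one of the following as the main analysis and use another as a sensitivity analysis:

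1. **Assignment at initiation.** Classify women when a suppressive regimen starts, whatever its later duration, with comparators matched on time since meeting the recurrent-UTI definition.
2. **Six-month landmark.** Count it from therapy start, and from the matched date in comparators. Require both cohorts to be alive, registered and outcome-free at the landmark, and count outcomes only afterwards. Do not count it from the date of meeting the recurrent-UTI definition, because women who start later would then be classed as comparators.
3. **Time-varying exposure.** Count each woman as unexposed until therapy starts and as exposed afterwards.

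The cost is wording and programming on registry data, with no new data collection. The landmark drops events in the first 6 months, which assignment at initiation keeps. Initiation must be recognised from prescription dates, since the article notes that diagnoses and treatments are not linked, so that rule needs to be written down as well.

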## Discussion

We expect to find inadequate management in a high percentage of UTI cases, considering that on many occasions patients are treated with second- or third-line antibiotic therapies with a preference for the longest regimens. Likewise, the use of suppressive antibiotic therapy as a prophylaxis in cases of recurrent UTI is expected to vary in our study.

In addition, we aim to determine whether women with recurrent UTIs treated with antibiotic suppressive therapy have a higher incidence and severity of potentially serious future infections, with special attention to acute pyelonephritis, urosepsis, COVID-19, and pneumonia, in comparison to women who are treated with antibiotics only when they present with a UTI.

All the information obtained in this first phase will allow us to continue with the following WPs of the project. Furthermore, if we find the inappropriate use of antibiotics, we will work on the creation of proposals to promote the correct treatment of UTIs in our environment according to clinical guidelines [40,41]. In this way, we will promote responsible management of UTIs in PHC among health care personnel and patients. In addition, our study will provide valuable information for health care policy makers and national programs to optimize the use of antimicrobials.

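### Suppressive therapy is counted only on a three-times-weekly schedule, so women on other long-term antibiotic schedules drop out of end point 5 and out of the exposed cohort in end point 6

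*Protocol article*

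**What the plan says.** All references are to the protocol article.

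- **Secondary End Points, item 5** asks for the percentage of women with recurrent UTI who received "suppressive therapy (ie, antibiotic treatment 3 times a week for 6 months or more", and for how long.
- **Item 6** splits women with recurrent UTI into those with suppressive therapy and "women with recurrent UTIs without suppressive therapy but with UTIs treated punctually", and compares infectious complications between them.
- **Item 7** draws a wider exposed group for pneumonia and COVID-19: "women with multiple antibiotic regimens for UTIs or suppressive therapy and women with UTIs treated punctually".
- **Introduction** speaks of "suppressive antibiotic treatment lasting more than 6 months to women who have repeated UTIs". It gives a duration and no weekly frequency.
- **Abstract (Conclusions)** and **Discussion** expect variation: "the use of antibiotic suppressive therapies, or prophylaxis, in recurrent UTIs will likely be highly variable" and "the use of suppressive antibiotic therapy as a prophylaxis in cases of recurrent UTI is expected to vary in our study".
- **Discussion** states the aim as suppressive therapy "in comparison to women who are treated with antibiotics only when they present with a UTI".
- **Data Collection and Data Sources** lists "prescriptions of PHC medical staff, with the corresponding pharmacy billing data" among the recorded information.

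**The concern.** Item 5 introduces its wording with the abbreviation for *that is*, so the weekly frequency is part of the definition and not an example. The open-ended part attaches to the duration, not to the frequency. A woman supplied continuously for a year on any other schedule therefore does not qualify.

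Two results depend on this rule. Item 5 is a prevalence, and it loses every such woman from its numerator. Item 6 is a cohort contrast, and it loses the same women from the exposed side. The article does not say where they then go. If they land among the women treated at episodes, long-term users sit in the reference group and the contrast moves toward no difference.

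**Working it through.** **1. Passages side by side**

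| Place | Duration | Weekly frequency |
|---|---|---|
| Introduction | over 6 months | none given |
| Secondary End Points, item 5 | at least 6 months | three times |

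The duration thresholds differ only at the boundary. The frequency condition is the material difference.

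**2. Where a long-term user on another schedule goes**

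- Item 5: not counted.
- Item 6, exposed cohort: not eligible.
- Item 6, comparator: two conditions apply, no suppressive therapy and episodes treated as they occur. She meets the first by definition. She could be read as meeting the second if her breakthrough episodes are treated. The Discussion's description of the comparator ("in comparison to women who are treated with antibiotics only when they present with a UTI") points the other way, and on that reading she is in neither cohort.
- Item 7: she may enter the exposed group through multiple antibiotic regimens.

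**3. Size**

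The article gives no rate, sample size or power for this comparison, so there is no figure of its own to reproduce. Every input below is an assumption.

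- S = true share of women with recurrent UTI on long-term suppression
- f = share of those on a schedule other than three times weekly
- True risk ratio RR = 1.5, taken as 15% versus 10%, with the same risk on every suppressive schedule

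Formulas:

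- Measured share in item 5 = S(1 − f), so the relative undercount equals f.
- Contamination if all missed women enter the comparator: c = Sf / (1 − S(1 − f)).
- Observed risk ratio = RR / (1 − c + c·RR).

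*Item 5, S = 20%*

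- f = 20%: 20% × 0.8 = 16%
- f = 60%: 20% × 0.4 = 8%

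*Item 6, S = 20%, all missed women in the comparator (per 100 women)*

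- f = 20%: 4 misplaced among 84. Comparator risk (80 × 10% + 4 × 15%) / 84 = 10.24%. Observed RR 15 / 10.24 = 1.465, about 1.47.
- f = 60%: 12 misplaced among 92. Comparator risk (80 × 10% + 12 × 15%) / 92 = 10.65%. Observed RR 15 / 10.65 = 1.408, about 1.41.

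*Wider range, same formulas*

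| S | f | Measured share, item 5 | c | Observed RR |
|---|---|---|---|---|
| 5% | 25% | 3.75% | 1.3% | 1.49 |
| 10% | 50% | 5% | 5.3% | 1.46 |
| 20% | 50% | 10% | 11.1% | 1.42 |
| 30% | 75% | 7.5% | 24.3% | 1.34 |

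*Item 6, missed women in neither cohort.* Then c = 0 and the ratio stays at 1.5 under the same assumptions. The cost is an exposed cohort smaller by the fraction f and a result that speaks only for three-times-weekly users.

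**The case against.** Several stronger readings are tempting, and the article does not carry them.

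- **That the Introduction defines the therapy by duration alone.** It describes a practice; its only formal definition there is of repeated UTI. A background sentence that omits frequency does not by itself contradict a methods definition that includes one. This stands. The two places differ and need reconciling, but the case rests on the literal rule in item 5.
- **That the plan itself expects schedules to vary.** The Abstract and Discussion speak of variable use, which may mean how often the therapy is prescribed, and neither mentions schedule. This also stands. It does not rescue the rule: how often long-term suppression is prescribed is still undercounted if other schedules occur.
- **That missed women necessarily dilute the contrast.** The comparator wording in item 6 and the Discussion make falling in neither cohort at least as likely. Dilution is conditional.
- **That the main adjusted analysis is affected.** The marginal structural model in Statistical Analysis is for the primary outcome and contrasts antibiotic exposure in general with none. As written, it does not use the three-times-weekly rule.
- **That the data source disqualifies the rule.** Billing records cannot show when doses were taken, but that limits any long-term exposure rule, including one based on supply. Prescriptions are also recorded, and item 4 plans to report dosage and duration.

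Multimedia Appendix 1 is not shown and may hold more detailed rules. Algorithm detail, such as permitted gaps in supply, may properly sit in the full protocol or analysis plan, and its absence is no fault here. Item 5, however, states a rule. If the fuller document is broader, the two must still be brought into line.

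**Conclusion.** The point holds for secondary end points 5 and 6. The definition as written excludes long-term users on any other schedule from the prevalence in end point 5 and from the exposed cohort in end point 6, and the article does not assign them elsewhere.

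The undercount in end point 5 is certain in direction if such women exist, and equals their share of all long-term users. Its actual size is unknown; the fall from 20% to between 16% and 8% rests on assumed inputs. The attenuation in end point 6 needs the further assumption that all missed women enter the comparator, and even then it is small to moderate. Whether three times weekly is the right schedule for patients is not judged.

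**What to change.** 1. Reconcile the Introduction and Secondary End Points into one exposure definition for analysis, including the duration boundary.
2. Classify long-term use by continuous prescribed or dispensed supply over the stated duration, whatever the weekly frequency.
3. Report the schedule descriptively within end point 5, where it can be recovered from prescriptions.
4. Keep the three-times-weekly group as a sensitivity analysis for end points 5 and 6.
5. State that women with long-term supply on any schedule are excluded from the comparator treated at episodes.

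The cost is a change of end point wording and a classification rule applied to prescription and billing data the study already plans to obtain. The exposed cohort becomes somewhat more heterogeneous, which the sensitivity analysis addresses. The change is best made before the cohorts are built.
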